## Abstract

**Background:**

Skin-to-skin contact (SSC) between mother and infant, commonly referred to as Kangaroo Mother Care (KMC), is recommended as an intervention for procedural pain. Evidence demonstrates its consistent efficacy in reducing pain for a single painful procedure. The purpose of this study is to examine the sustained efficacy of KMC, provided during all routine painful procedures for the duration of Neonatal Intensive Care Unit (NICU) hospitalization, in diminishing behavioral pain response in preterm neonates. The efficacy of KMC alone will be compared to standard care of 24% oral sucrose, as well as the combination of KMC and 24% oral sucrose.

**Methods/design:**

Infants admitted to the NICU who are less than 36 6/7 weeks gestational age (according to early ultrasound), that are stable enough to be held in KMC, will be considered eligible (N = 258). Using a single-blinded randomized parallel group design, participants will be assigned to one of three possible interventions: 1) KMC, 2) combined KMC and sucrose, and 3) sucrose alone, when they undergo any routine painful procedure (heel lance, venipuncture, intravenous, oro/nasogastric insertion). The primary outcome is infant’s pain intensity, which will be assessed using the Premature Infant Pain Profile (PIPP). The secondary outcome will be maturity of neurobehavioral functioning, as measured by the Neurobehavioral Assessment of the Preterm Infant (NAPI). Gestational age, cumulative exposure to KMC provided during non-pain contexts, and maternal cortisol levels will be considered in the analysis. Clinical feasibility will be accounted for from nurse and maternal questionnaires.

**Discussion:**

This will be the first study to examine the repeated use of KMC for managing procedural pain in preterm neonates. It is also the first to compare KMC to sucrose, or the interventions in combination, across time. Based on the theoretical framework of the brain opioid theory of attachment, it is expected that KMC will be a preferred standard of care. However, current pain management guidelines are based on minimal data on repeated use of either intervention. Therefore, regardless of the outcomes of this study, results will have important implications for guidelines and practices related to management of procedural pain in preterm infants.

**Trial registration:**

ClinicalTrials.gov Identifier: NCT01561547.

## Background

Even in the context of critical care, mothers can provide comfort to their preterm neonates during painful procedures. Skin-to-skin contact (SSC), commonly referred to as Kangaroo Mother Care (KMC), is recommended as an intervention for procedural pain in guidelines by the Canadian Pediatric Society and the American Academy of Pediatrics [1]. There are now more than 18 studies showing consistent efficacy of KMC in reducing pain from a single painful procedure [2,3]. These same guidelines also recommend 24% oral sucrose for common procedural pain based on more than 57 studies [4]. Despite some concerns with the influence of sucrose on neurodevelopmental outcomes [5,6], sucrose is considered standard care for management of procedural pain in most Neonatal Intensive Care Units (NICUs) [7].

It is assumed that KMC, shown to be effective for managing pain in neonates during single events, will remain efficacious over time. However, as no studies have examined its repeated use, this is unknown. In addition, as the mechanism underlying oral sucrose and KMC are thought to differ (sweet taste is believed to release endorphins and KMC believed to release oxytocin), the interventions could have synergistic effects when used in combination. The purpose of this study is to examine the sustained efficacy of KMC in diminishing pain response in preterm neonates compared to standard care of oral sucrose, as well as examine the combination of KMC and oral sucrose. Infant’s neurodevelopment at term equivalence will also be compared between groups.

## Summary of literature review

### Pain in the NICU

More than two decades ago, two Canadian surveys examining pain and its management in the NICU reported under-treatment of procedural pain [8,9]. These surveys indicated that unlike post-operative pain, which is typically treated with analgesic intervention, management of procedural pain using analgesia was uncommon. In these surveys, the number of tissue damaging procedures was documented as averaging from 2 to 8 per infant [8]. The findings of these Canadian surveys are consistent with the findings of surveys conducted in the US [10,11] and UK [12].

More recently, surveys conducted in Canadian, Dutch, and French NICUs indicate that infants undergo a similar number of procedures with almost 50% of all tissue breaking procedures associated with little or no analgesia [13-15]. The under management of pain noted within the literature has been reported in spite of guidelines recommending analgesia and comfort measures in neonates undergoing medical procedures [1], as well as the fact that most neonatal staff believe that infants are capable of experiencing pain from a very early age [13].

### Treatment of procedural pain

#### *Pharmacologic agents*

Pharmacologic agents that have been examined for reducing procedural pain in neonates include topical anesthetics and systemic drugs, such as opioids or acetaminophen. Topical anesthetics, while effective for pain management during circumcision [16-20], have been shown to be ineffective for heel lance, venipuncture, and insertion of intravenous lines [21-25]. Systemic drugs, specifically opiates, are highly sensitive to the developmental stage of the infant [26,27]. Therefore, rapid changes in requirements make effective and safe dosing a challenge. In addition, opiates have significantly slower clearance in neonates [28-32], and have not necessarily been demonstrated as effective for managing procedural pain [33]. Trials of acetaminophen for procedural pain control have demonstrated that it is not effective, and may even be no better than placebo for heel lance procedure [34,35]. Thus, pharmacological management for common, repeated, painful procedures in preterm neonates is not an option. Given the frequency of painful procedures in NICUs, the short and long term negative effects of repeated pain exposure in this population, and the ethical imperative to manage this pain, other approaches are required.

#### *Alternative methods of procedural pain control*

Non-pharmacological approaches to pain management are thought to be based on the release of endogenous opiates [36,37]. Although there are scant data in neonates regarding endogenous descending inhibitory mechanisms, the engagement of mechanisms that release endorphins is well established in adults [36,37]. Animal studies suggest that the endogenous system is not well developed prior to 32-weeks post-conception, however, there is speculation that it may be developed enough to provide some level of comfort [38,39]. Various non-pharmacological strategies for pain control have been tested in neonates and show varying degree of efficacy. These strategies can be categorized into sensory stimulation [40,41] (i.e., positioning/swaddling, vestibular action/rocking, non-nutritive sucking, music), nutritive [42-63] (i.e., breastfeeding, oral sweet solutions), and maternal interventions (i.e., maternal odor and voice, breastfeeding, KMC). For the purposes of this trial, KMC and 24% oral sucrose (considered standard care) are the interventions of interest.

#### *Sucrose*

Research in animals and human infants have shown that intra-oral sucrose solutions have an analgesic effect. Studies using sucrose for pain relief started in the late 1980’s [50-52] and have since included both term and preterm infants. Sucrose, the oral solution used most frequently, has been examined in two systematic reviews [50,62], and one meta-analysis [4]. These reviews are in agreement regarding the positive efficacy of oral sucrose for reducing procedural pain in preterm neonates.

Infant response to interventions has been assessed using both behavioral (e.g., cry and facial action) and physiological indicators, as well as composite measures of pain. A recent study demonstrated that although sucrose decreased scores on the Premature Infant Pain Profile (PIPP), there was still nociceptive activity in the somatosensory cortex [63]. Given the dissociation between the affective components of pain [64-66], that is how much it hurts (somatosensory cortex) vs. how aversive it is (frontal and pre-frontal cortex), it is likely that it is the affective component of the pain response that is being modified by sucrose. The authors of the study thus raised concerns about the analgesic properties of sucrose, and whether it can ameliorate the adverse effects of repeated pain exposure. Such findings reinforce the need for continued study of other non-pharmacological interventions such as KMC alone or in conjunction with sucrose.

The effect of sucrose on pain intensity on consecutive days has been addressed, but needs further investigation. While one study examining the use of sucrose for all painful procedures in the first week of life in the NICU reported poorer neurodevelopmental outcome scores with higher doses of sucrose [6], a secondary analysis found that this was only the case in infants who received more than 10 doses over 24 hours [67]. Concerns about the long-term use of sucrose on neurodevelopmental outcomes have also been raised by Holsti and Grunau [5]. They provide a strong and logical argument that the development of the infant’s dopaminergic system is altered with sucrose administration. Specifically, that sugar stimulates dopamine release, and that this release responds or is a reaction to the concentration of sucrose rather than the volume. In addition to this argument, there is also a relationship between dopamine and attention and motor development – the specific neurodevelopmental outcomes used in the study examining repeated sucrose administration [6]. Holsti and Grunau suggest that dopamine regulation is disturbed by receiving repeated doses of 24% sucrose (the recommended concentration for procedural pain management in neonates), and that this interferes with attention and motor development.

#### *Kangaroo Mother Care*

Kangaroo Mother Care (KMC) was implemented in the modern era as an alternative to incubator care to maintain preterm infants’ body temperature and increase survival rates in South America due to short supply of incubators [68]. During this time, it was serendipitously noted that infants in KMC spent more time in quiet sleep state [69,70]. As quiet sleep state is associated with decreased pain response [71,72], the idea developed to use KMC to control procedural pain. When initially studied in full term neonates, decreased crying and heart rate acceleration was observed [73]. Subsequent studies in preterm neonates showed decrease in facial action, decrease in heart rate acceleration, and increased oxygen saturation, with a decrease in overall pain scores [74].

In a recent Cochrane review of the literature on skin-to-skin contact for procedural pain in infants conducted by the authors of this protocol [3], 13 studies that met the inclusion criteria showed positive results. Interestingly, two of the studies [75,76] showed that KMC was more efficacious than sweet taste in reducing infant’s procedural pain. However, to our knowledge, there have been no published studies to date examining the combined efficacy of KMC and sucrose in managing procedural pain in preterm infants.

**Mechanism underlying KMC as a comfort strategy** There are likely several mechanisms underlying the specific pain-relieving effect of KMC. One hypothesis that could be related to all non-pharmacological strategies is derived from the Gate Control Theory of Melzack and Wall [36]. According to this theory, stimuli travelling ascending pathways may inhibit the nociceptive signals from painful stimulus through various endogenous mechanisms located along the spino-thalamic tract [77]. The stronger these competing stimuli are, including multiple modalities, the more effective they are at blocking the perception of pain. Such theories help explain why multiple modalities, such as KMC, breastfeeding, or sensorial saturation that involves tactile, auditory, and olfactory mechanisms are more effective than single modalities.

The mechanism of the comforting effect of breastfeeding and KMC is likely related to the release of oxytocin [78,79]. Oxytocin has been referred to as the love hormone due to its role in affiliative behaviors [80-83]. In an animal model of pain and oxytocin, massage-like stroking induced acute antinociception that was reversed by an oxytocin antagonist [84]. Also, when oxytocin was injected into the periaqeductal gray region, it had an antinociceptive effect.

In summary, 1) procedural pain in the NICU is infrequently and poorly managed, 2) pharmacological interventions present problems with this population, 3) among non-pharmacological interventions both sucrose and KMC are supported by numerous studies as one-time interventions in diminishing pain response, 4) there are no studies of repeated use of KMC and only two studies that have followed infants for repeated use of sucrose over time have had conclusive results, 5) no published studies to date have examined the combination of KMC and sucrose across time.

Given the findings of research to date, this study proposes that KMC alone or in combination with sucrose will continue to reduce pain across the NICU stay more than sucrose alone. This is based on the belief that the touch and olfactory senses invoked from the mother are fundamental to the maternal role of affiliation and comfort through underlying mechanisms of hormone release. It is further proposed that neurodevelopment will be better in infants who have received KMC for minor painful procedures due to the release of norepinephrine during KMC.

### Theoretical framework

Nelson and Panksept’s Brain Opioid Theory of Social Attachment provides the conceptual framework for this study [79]. This theory, based on animal experimentation, postulates that maternal touch, smell, (and milk) release endogenous opiates, which are known to reduce pain and promote affiliative behaviors. There are other hormones involves in mother-infant attachment and comforting, namely oxytocin and epinephrine. Oxytocin, as described above, is the primary hormone promoting affiliation, is released with social contact, and also appears to have antinociceptive effects [84].

### Hypotheses

The hypotheses of this study are as follows:

i. Pain response to heel lance or venipuncture for blood sampling, as measured by the Premature Infant Pain Profile (PIPP), will be lower by 1.5 points in KMC alone than sucrose alone. The combination will be marginally better (0.5 on PIPP scale) for a total of 2 points between combination and sucrose alone and 0.5 points between KMC alone and combination.

ii. This difference in PIPP scores will remain across the infant’s hospitalization.

iii. Neurodevelopmental sub-scores of the Neurobehavioral Assessment of the Preterm Infant (NAPI) of 1) motor development and vigor and 2) alertness and orientation at discharge from the NICU will be significantly higher in infants in the KMC groups than the sucrose alone group.

A no-treatment control group will not be used in this study, as it is believed to be unethical given that it has been argued that a state of equipoise has been reached with sucrose [85], and it is considered the standard of care. According to the hypotheses listed above, it is proposed that KMC will be a preferred standard of care.

## Methods

### Trial design

TRAKC is a single-blinded, randomized, parallel group design (Figure 1). The coders assessing the data will be blind to group assignment; however, the person completing the blood sampling will not be blind as it is impossible to prevent them from knowing participant KMC condition (i.e., skin-to-skin or incubator care).

**Figure 1 F1:**
[figure not shown]
TRAKC Trial CONSORT Flow Diagram.

### Participants

The sample will consist of 258 infants born less than 36 6/7 weeks gestational age according to the early ultrasound, that are stable enough to be held in KMC, whose mothers consent and expect to be available for KMC. Determination of infant physiological stability will be confirmed by the attending neonatal staff. Infant exclusion criteria are major congenital anomalies, receiving narcotics, or surgery. Infants will be enrolled within 5 days of birth.

### Sample size

The primary analyses of this study will be hierarchical linear modeling (growth curve analysis). Given that there are no acceptable methods for calculating sample size for this design, sample size estimates are based on Repeated Measures Analysis of Variance (RM-ANOVA). As a slope is being proposed in this study, with between group differences being specified, then across the slope (time), the between group differences will remain the same and thus the sample size should be the same at any point in time. In studies using RM-ANOVA, the sample size is based on group differences, and a similar principle applies. Given this, a sample of 258 will provide a power of 0.9 to detect a difference of 1.5 points (considered to be a clinically significant difference) with a standard deviation of 3 on the PIPP.

### Study setting

The study setting is the NICU of a tertiary-level Canadian hospital specializing in women and children’s health. Enrollment began in July of 2012, and is expected to be completed within 42 months of initiation.

### Randomization

#### Sequence generation

Group assignment will be determined using a password protected website, where randomization is in permuted blocks and participants will be stratified by gestational age (less than or greater than/equal to 32 weeks gestational age at birth) in order to ensure equal distribution across groups for all ages.

#### Implementation

Group assignment will be acquired by the research nurse from the secure website. The REB approved research nurse is the only individual in this study who has access to the secure site after consent is obtained.

### Allocation concealment mechanism

The pharmacy at the study site will supply the syringes containing the study solution. Of the study syringes, 1/3 will contain sterile water and 2/3 will contain 24% sucrose. The study solutions will be labeled with a code known only by pharmacy and the research nurse. Solutions will be prepared and packaged in an identical matter. Upon knowing infant group assignment, the research nurse will label each syringe with the infants study number and name to ensure added protection. Each participant will be provided syringes at his/her bedside and the research nurse will conduct regular syringe counts to evaluate compliance.

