### Procedures

Documented approval has been obtained from the REB of the study site. When an eligible infant becomes available, the research nurse will explain the study to the parents, answer questions, determine the mother’s availability to provide KMC, and obtain written informed consent.

A minimum of 3 painful procedure sessions will be video-recorded with each infant, with each session being a minimum of 24-hours apart. For infants less than or equal to 32 weeks, sessions will be recorded as close to recruitment as possible, at 32 weeks, 36 weeks, and prior to discharge. For older infants, the sessions will be spaced as evenly apart as can be estimated. The research nurse will coordinate the timing of the procedure-recording with the staff, call parents to tell them that the procedure is taking place at a given time, and tell them the KMC condition (i.e., skin-to-skin or standard care).

The research nurse will mark phases on the recordings by holding colored cards briefly in front of the video camera. These phases will include baseline 1 at beginning of monitoring, baseline 2 prior to procedure initiation, heel warming or vein site cleansing, painful procedure (i.e., heel lance or venipuncture), application of bandage, and heart rate return to baseline. The research nurse will ensure that monitoring remains intact, and that the camera is focused on the infants face at an angle that makes the infant appear prone in an incubator in order to keep coders naïve [74]. Phases will be matched to the built in timer of the Somte monitor used to record physiologic data.

Depending on the gestational age of the infant, neurodevelopmental assessments using the Neurodevelopmental Assessment of the Preterm Infant will be conducted at 32 weeks, 36 weeks, and/or term equivalence by a trained research assistant who will be kept blind to group assignment.

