### Intervention conditions

#### *KMC condition*

If the infant is randomized to the KMC condition, the research nurse will begin by recording a one-minute sample of the infant in the incubator. The research nurse will then place the mother and infant into the KMC condition, where the diaper-clad infant is help upright, at an angle of approximately 60°, between the mothers breasts, providing maximal skin-to-skin contact between mother and baby. The infant will remain in KMC for at least 15 minutes prior to the painful procedure. Two minutes prior to the procedure the infant will receive ¼ of the recommended (based on NICU protocol) volume of sterile water by syringe onto the tongue. The remainder of the total recommended dose will be given as needed in small increments during the procedure.

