#### *Combined KMC and sucrose condition*

For combined sucrose and KMC, the infant will be placed in KMC as described for the KMC alone condition, however, will receive 24% oral sucrose solution as per the NICU protocol described above.

Although most painful procedures will not be video-recorded for the study analysis, the expectation is that the staff caring for infants enrolled in the study will follow the study intervention protocol for all painful procedures, and that any deviations from the study protocol will be charted and included in the analyses. Babies in the KMC group will have reminder signs at the bedside prompting the staff to place them in KMC for procedures, and the study syringes of either 24% sucrose solution or sterile water will be available to staff at the bedside throughout the infant’s stay in the NICU. Staff documentation of all painful procedures will be monitored to ensure compliance with the study protocol.

In order to ensure equipoise, staff may deviate from the protocol to give off-study doses of rescue sucrose if the infant has a PIPP score > 6 (considered to indicate pain) at their discretion. The deviations from protocol will be recorded on a procedure record kept at each infant’s bedside. If the mother is unavailable for a painful procedure, the infant will be swaddled and given the study solution. If the infant has a PIPP score > 6, off-study sucrose may be given by the nurse caring for the patient. All off-study sucrose doses will be recorded in the procedure record and the research nurse will confirm the doses given from the medication administration record.

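### The research nurse who runs the recorded sessions also holds the solution code, so water versus sucrose in the two KMC arms is unmasked to that role without need

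*Protocol article*

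**What the plan says.** All references are to the protocol article.

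- **Solution code** (Allocation concealment mechanism): "The study solutions will be labeled with a code known only by pharmacy and the research nurse". Syringes are packaged identically; one third hold sterile water and two thirds 24% sucrose.
- **Assignment** (Randomization, Implementation): "Group assignment will be acquired by the research nurse from the secure website", and "The REB approved research nurse is the only individual in this study who has access to the secure site after consent is obtained".
- **Labelling** (Allocation concealment mechanism): once the assignment is known, "the research nurse will label each syringe with the infants study number and name to ensure added protection".
- **Recorded sessions** (KMC condition; Procedures): "The research nurse will then place the mother and infant into the KMC condition", and "The research nurse will mark phases on the recordings by holding colored cards briefly in front of the video camera". The same role agrees the timing with staff, calls the parents, and looks after the monitoring and the camera angle.
- **Declared blinding** (Trial design; Procedures; Outcomes): the trial is single-blinded. The PIPP coders are blind and work outside the NICU, and the NAPI assessor is kept blind. The person taking the blood sample is not blind, because skin-to-skin or incubator care can be seen.
- **Discretionary steps** (Intervention conditions): "The remainder of the total recommended dose will be given as needed in small increments during the procedure"; and, when the PIPP score exceeds 6, "staff may deviate from the protocol to give off-study doses of rescue sucrose".

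**The concern.** Two of the three comparisons set KMC against no KMC, and anyone at the bedside can see that difference. KMC alone versus KMC plus sucrose is the exception: both groups are held skin-to-skin and both receive a study solution from an identical syringe. It is the one contrast in which the people at the bedside could be masked. It is also a stated hypothesis (0.5 PIPP points) and part of the third research question in Statistical analysis.

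The plan gives up that masking in the role closest to the recording. A nurse who knows that an infant is on water may settle or position the infant differently, time the session differently, or say something that affects how staff use the remaining solution or off-study sucrose. Extra support or sucrose for the water infants would pull the contrast toward zero. Expectation that the combination is better could push it the other way. Neither effect is visible to a blind coder, because the behaviour being coded would itself have changed.

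**Working it through.** **Step 1. What the session runner knows.** Implementation gives the nurse the three-arm assignment, and Allocation concealment mechanism gives the nurse the code. Either alone is enough to tell water from sucrose in a KMC infant. Procedures and KMC condition put the same role in the recorded session.

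**Step 2. What the session runner needs.** Solution-giving follows one pattern in the three arms: a quarter of the recommended volume two minutes before the procedure, the remainder as needed. What differs visibly is KMC or no KMC. Procedures already works at that level when the nurse tells parents only whether the session is skin-to-skin or standard care. Syringe counts and the check of off-study doses against the medication record do not need the code either. The one task that uses it is matching syringes to infants, and pharmacy also holds the code.

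**Step 3. The reason given for not blinding.** Trial design refers to the person taking the sample and to the visible KMC condition. That covers KMC versus no KMC. It does not cover water versus sucrose within KMC.

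**Step 4. The plan's own figures.** The article does not state the allocation ratio; assume three equal arms.
- Infants per arm: 258 / 3 = 86.
- Water: 86 / 258 = 1/3. Sucrose: 172 / 258 = 2/3. Both agree with the stated syringe split. Within the KMC arms, half the infants are on water (86 / 172).
- Sample size, assuming two-sided alpha 0.05: n = 2 × 3² × (1.960 + 1.282)² / 1.5² = 84.1, rounded up to 85 per arm, or 255 in total against 258 stated. With 86 per arm the power is 0.906 against 0.9 stated.

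None of these figures changes because of this point.

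**Step 5. Illustrative size, one route only.** The route is unequal off-study sucrose. Let d be the excess proportion of KMC-alone sessions with off-study sucrose that is due to unblinding, and e the effect of sucrose on a score in an infant already in KMC. Then shift = d × e. The documents give no d; 0.10 and 0.25 are assumptions. For e, the closest figure in the protocol is the hypothesised 0.5 points between KMC alone and the combination.

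| d | shift with e = 0.5 | share of the 0.5-point contrast |
|---|---|---|
| 0.10 | 0.10 × 0.5 = 0.05 | 10% |
| 0.25 | 0.25 × 0.5 = 0.125 | 25% |

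For scale, the standard error of this contrast at one time point is 3 × √(2/86) = 0.46. The shifts are 0.05 / 0.46 = 11% and 0.125 / 0.46 = 27% of one standard error. Changes in how the nurse handles the session are not captured here, and the documents give nothing from which to size them.

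**The case against.** The strongest reply is that nothing declared is contradicted. The article calls the trial single-blinded, names the coders as blind, and never says the research nurse is. Coding is done off the unit by people naive to the study's purpose. The phases the nurse marks are mostly observable events matched to the monitor's timer. Off-study sucrose is decided by clinical staff who are not given the code, and deviations are charted and carried into the analysis. Sterile water also equalises oral volume and what coders see on the video, whatever the nurse knows. The powered contrast, 1.5 points, is not affected. The nurse also has a task, labelling, that uses the assignment.

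Most of this stands, and it limits the point to a modest one. Two parts do not dispose of it. Labelling explains why the nurse holds the code but not why this role must do the labelling. Charting off-study doses, or adjusting for total sucrose doses, does not remove a bias that arises after randomization and from knowledge of the arm.

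Three stronger readings are tempting and are not supported:

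- **That the blind within the KMC arms cannot hold.** The declared blinds stay intact. Bedside staff and mothers are not given the code.
- **That staff can read the code off the sucrose-alone infants.** This would follow if there were one code per solution, since every infant without KMC receives sucrose. The article says only that there is a code, and the syringes also carry the infant's own number and name. A code per infant fits the text equally well and reveals nothing across infants.
- **That unblinding could erase the 0.5-point contrast.** At d = 0.25 this needs e = 2 points (0.25 × 2 = 0.5). The protocol's own figure for sucrose added to KMC is 0.5, and with that figure d would have to be 1. Off-study sucrose also follows an observed score above 6, so it need not alter the score already being recorded.

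**Conclusion.** The point holds in a limited form. The article fixes an arrangement in which the person running the recorded sessions knows water from sucrose in both KMC arms, with no stated reason and no practical need. The consequence is a possible performance bias in KMC alone versus the combination, of uncertain direction and of a size the documents do not determine. The 0.05 to 0.125 points illustrates one route; it rests on assumed excess use of 10 to 25 percentage points and on the protocol's 0.5-point difference as the effect of added sucrose. Masking of bedside staff would fail only if the code is disclosed or shared across infants, and the article states neither. The case for change is that the weakness is avoidable and cheap to remove, not that the trial's conclusions are endangered.

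**What to change.** 1. Have the website return to the research nurse only KMC yes or no and a participant-specific kit number, and amend Implementation to match.
2. Have pharmacy hold the list linking kit numbers to contents and dispense identical syringes already labelled with the infant's study number. The nurse can still add the infant's name and do the syringe counts.
3. In Allocation concealment mechanism, remove the research nurse from those who know the code, and say that kit numbers are unique to the infant. This also settles the shared-code question.
4. In Trial design, state that the session runner is masked to the solution in the KMC arms. Enrollment has begun, so record the date from which this applies.

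The cost is a change to the website output and slightly more labelling work for pharmacy, including resupply under the same number during long stays. No arm, dose, session, outcome or sample size changes.
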